## Analysis

We will apply our experience in creating and maintaining large data sets from multi-site studies to assure that the data obtained in the proposed study are of high quality. We begin our analyses by looking descriptively at the variables to be used and assessing the extent to which the assumptions of the proposed models are violated. Further, measurement models that have already been developed in prior studies will be evaluated in the data set using confirmatory techniques. For those constructs for which the measurement has not been previously validated, psychometric analyses will be conducted to provide strong grounds for conducting the proposed outcome analyses. We recognize the importance of addressing the nested data structure in the measurement as well as analysis of outcomes (James, 1982; Sirotnik, 1980). Psychometric analyses appropriate for the multilevel structure of the data will be used when evaluating the measurement of individual level variables (James, 1982; Kreft, 1993; Muthén, 1989, 1991, 1994; Raudenbush et al., 1991; Sirotnik, 1980).

The analysis of intervention effects on youth outcomes must incorporate the nesting of individuals within communities and the random assignment to conditions at the community level. Thus, the analyses need to incorporate multilevel models that take this nesting into account and provide unbiased estimates of standard errors (Bryk et al., 1996; Hox, 1998; Murray, 1998). The CTC intervention is expected to produce community-level changes in prevention service system characteristics, for example, increased collaboration among service providers and increased use of science-based prevention strategies. These changes in service systems characteristics are expected to produce student-level changes in risk and protective factors. These changes in risk and protective factors are expected, in turn, to affect changes in self reported adolescent drug use and related problem behaviors. The sections below describe both cross sectional and longitudinal comparisons of intervention and control communities.

**Aim 1.** To test the effectiveness of the CTC system in reducing risk, increasing protection and reducing problem behaviors.

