Analyses of the effects of intervention on adolescent drug use and related behavior will be conducted using logit models that assess the effects of the intervention on the likelihood that children within each community engage in each of the targeted behaviors, initiation of alcohol, cigarette, and marijuana use, and incidence of delinquent and violent behavior. For example, we can begin analyses looking at the effects of intervention on reported alcohol use, a child level dependent variable at a single time point. A three level model in which children's reported alcohol use is treated as nested within community, and community is nested within the matched pair, will be used. The intervention will be considered a fixed effect at level 2. Again, in some models, school, instead of the matched pair, will be entered as a level. Analyses also will seek to assess intervention effects on growth in alcohol use across grades by combining grade level samples and entering grade as a covariate at the child level 1. This model can then be used for a longitudinal assessment of the effects of intervention on changes over time in the prevalence of alcohol use at the community level. Using HLM (Bryk & Raudenbush, 1992; Bryk et al., 1996) terminology and a logit link to model the binary outcome the model would be written:

|                           |                                                                                                                                                                                            |
|---------------------------|--------------------------------------------------------------------------------------------------------------------------------------------------------------------------------------------|
| Level-1, students         | Probability of alcohol use ( $Y = 1$ ) = $\phi_{ijkp}$
$\log(\phi_{ijkp}/1 - \phi_{ijkp}) = \pi_{0jkp} + \pi_{1jkp} \text{Grade}$                                                       |
| Level-2, survey occasions | $\pi_{0jkp} = \beta_{00kp} + \beta_{01kp} \text{Year} + r_{0jkp}$
$\pi_{1jkp} = \beta_{10kp}$                                                                                           |
| Level-3, communities      | $\beta_{00kp} = \gamma_{000p} + u_{00kp}$
$\beta_{01kp} = \gamma_{010p} + \gamma_{011p} \text{Treatment} + u_{01kp}$
$\beta_{10kp} = \gamma_{100p} + \gamma_{101p} \text{Treatment}$ |

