| Level-4, pairs            | $\gamma_{000p} = \zeta_{0000} + w_{000p}$
$\gamma_{010p} = \zeta_{0100} + w_{010p}$
$\gamma_{011p} = \zeta_{0110} + w_{011p}$                                                        |

$$\gamma_{101p} = \zeta_{1010} + w_{101p}$$

This model postulates that the probability of an individual reporting alcohol use is a function of their grade and the average alcohol use at time  $j$  in community  $k$  within pair  $p$ . The growth portion of the model occurs at level 2, in which the proportion of youth within each community at a given time point using alcohol is modeled as a function of the initial alcohol use in that community and the slope related to the year of observation. At the community level, the effect of the intervention on change within communities and the relationship of grade to alcohol use is tested. Note that this is actually testing the interaction of the linear growth component with treatment and of the relationship of grade to outcomes with treatment. This is true because the model postulates that the slope of the growth curve varies as a function of treatment, the definition of an interaction. These four level models will be modeled in MLwiN (Rasbash et al., 2000), which allows for more than three levels of nesting.

Given that not all of the risk and protective factors are expected to be normally distributed, the assumption of normal and independently distributed errors within each level of nesting may not be appropriate (Feng et al., 2001). Permutation tests which do not make this assumption are available in group-randomized designs. The appropriateness of using these models will be examined. It is also possible to pose models other than growth models in testing the relationship of the intervention to change in outcomes. While we believe that growth models are reasonable, given that exposure will increase and services are expected to improve over the course of the study, thus improving outcomes, the fit of these models will be examined and other options considered if necessary.

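### The Grade-slope equation of the four-level logit model has no community residual, so its Treatment × Grade test is valid only under a specification the protocol does not show

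*Protocol*

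**What the plan says.** The Analysis section asks for "multilevel models that take this nesting into account and provide unbiased estimates of standard errors". Under Aim 1, Cross-sectional cohort analyses, the binary-outcome model is then written out for alcohol use, with students, survey occasions, communities and matched pairs as its four levels.

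The equations that matter here are:
- **Year slope, communities:** "\beta_{01kp} = \gamma_{010p} + \gamma_{011p} \text{Treatment} + u_{01kp". It ends in a community residual, as does the intercept equation (`u_00kp`).
- **Grade slope, survey occasions:** "\pi_{1jkp} = \beta_{10kp". There is no residual.
- **Grade slope, communities:** "\beta_{10kp} = \gamma_{100p} + \gamma_{101p} \text{Treatment". There is no residual.
- **Treatment × Grade coefficient, pairs:** "\gamma_{101p} = \zeta_{1010} + w_{101p". This is a pair-level random term.

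No pair-level equation for `gamma_100p` can be seen.

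The Grade contrast is one of two intervention effects tested. The section announces it: "Analyses also will seek to assess intervention effects on growth in alcohol use across grades by combining grade level samples". The paragraph after the equations describes the model as "testing the interaction of the linear growth component with treatment and of the relationship of grade to outcomes with treatment".

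**The concern.** Two tests of the same intervention, at the same level of the same model, have different error structures, and no reason is given. Communities will differ to some degree in how steeply use rises from grade 6 to grade 12, whatever CTC does. With 12 communities per arm, that variation belongs in the standard error of Treatment × Grade. If it enters only through a term that multiplies Treatment, it may be counted for the intervention communities and not for the controls. Part of the ordinary difference between communities could then be reported as CTC flattening the grade gradient.

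**Working it through.** **Inputs from the protocol.** There are 12 pairs with one community per arm, four grades (6, 8, 10, 12) and three study surveys. About 221 usable surveys are expected per grade and community (316 × 0.70 = 221.2, which reproduces the stated figure). Eighth-grade prevalences and detectable differences are in Table 3. The protocol gives no error rate or power for Treatment × Grade, so there is no stated figure to reproduce.

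**Assumptions.** Two-sided 5% test; average p(1−p) of 0.22; between-community SD of the Grade slope τ.

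**Step 1: sampling error of one community's Grade slope.** Squared grade deviations from 9 sum to 9 + 1 + 1 + 9 = 20, or 60 over three surveys. So v = 1/(221 × 0.22 × 60) = 0.000343 and the SE is 0.0185 logit per grade. Starting instead from the grade-8 prevalence of 0.52, with assumed gradients of 0.2–0.5 logit per grade, gives 0.018–0.023.

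**Step 2: what each reading does to the variance of a within-pair slope difference.** If slopes are uncorrelated within pairs, the true variance is 2v + 2τ².

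- *Reading 1: `gamma_100p` is one constant, Treatment coded 0/1.* Controls get v and intervention communities v + τ², so the model uses 2v + τ². The ratio to the truth is (2v + τ²)/(2v + 2τ²). At τ² = v it is 3/4; the effective cut-off is 1.96 × √0.75 = 1.70 and the rejection rate 9.0%. As τ grows the ratio tends to 1/2, the cut-off to 1.39 and the rate to 16.6%. Estimating the variance from 12 pairs adds a little. If half of τ² is shared within pairs, the true variance is 2v + τ², which is what the model uses, so this source of inflation vanishes.
- *Reading 2: `gamma_100p` has its own pair term, variance a, independent of `w_101p`, variance b.* The model implies control variance v + a and within-pair covariance a. Uncorrelated slopes need a = τ² for the first and a = 0 for the second. Both cannot hold.
- *Reading 3: the same, with a free covariance c.* Control variance is v + a, intervention variance v + a + b + 2c, covariance a + c. Setting a = τ², c = −τ², b = 2τ² fits exactly, and the difference has variance 2v + b = 2v + 2τ². Coding ±1/2 also makes `w_101p` the free within-pair error.

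**Step 3: simulated rejection rates with no treatment effect** (normal approximation at slope level, 12 pairs, not a full four-level logit fit):

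| Reading | Slopes within pairs | Slope SD | z | t, 11 df |
|---|---|---|---|---|
| 1 | uncorrelated | 0.01 | 6.2% | 3.6% |
| 1 | uncorrelated | 0.02 / 0.03 / 0.05 | 10.0 / 13.0 / 16.0% | 6.6 / 9.2 / 11.8% |
| 1 | half shared | 0.02 / 0.03 / 0.05 | 5.9 / 6.4 / 6.8% | 3.5 / 4.0 / 4.3% |
| 2 | uncorrelated | 0.0185–0.06 | 8–13% | 6–8% |
| 2 | half shared | 0.0185–0.06 | 8–9% | not tabulated |
| 3 | uncorrelated | 0.02 / 0.03 / 0.05 | 7.0 / 7.6 / 7.6% | 4.5 / 5.0 / 5.0% |

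At a slope SD of 0.06, reading 1 with uncorrelated slopes gives about 17% (z) and 13% (t, 11 df). The excess under reading 3 comes from using z with 12 pairs, not from a missing term.

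**Step 4: is a slope SD of 0.02–0.06 plausible?** Table 3 gives only indirect evidence, for grade 8. Take SE = detectable difference/(t.975 + t.80) on 10 df, where the two quantiles sum to about 3.107, and residual community variance = 6·SE² − p(1−p)/221. For lifetime alcohol, 0.130/3.107 = 0.0418; 6 × 0.0418² − 0.2496/221 = 0.0094; the SD is 0.097, or 0.097/0.2496 = 0.39 logit. Lifetime cigarettes give 0.21 logit and 30-day alcohol 0.27.

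If such deviations are independent between grades, the slope SD is 0.21/√20 to 0.39/√20 = 0.047–0.09 when they persist over surveys, or 0.21/√60 to 0.39/√60 = 0.027–0.05 when they do not. A between-grade correlation of 0.5 multiplies these by √0.5 = 0.71. A correlation of 0.8 multiplies them by √0.2 = 0.45, which gives about 0.012–0.04.

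**The case against.** A reader might infer from the printed line alone that all 12 control communities are forced to share one Grade slope and that false positives double or triple. The protocol does not support that.

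- `gamma_100p` carries a pair subscript, and every other pair-subscripted coefficient shown has its own pair-level equation with a random term. The `gamma_100p` row would fall where the table breaks, so its absence from the text available here cannot be counted as an omission. That stands.
- With one community per arm in each pair, a pair-varying Treatment × Grade coefficient can itself be the correct matched-pair error (reading 3). That stands too, but it needs a free covariance or ±1/2 coding, neither of which is stated. Restoring the row with an independent pair term does not cure the problem (reading 2).
- The size depends on an assumed slope SD and on slopes being dissimilar within pairs, although the protocol says matching reduced error variance for most outcomes. This is why the figures above are scenarios.
- The model is offered as an example. Permutation tests and model fit are to be examined, and an adviser will help to specify the multilevel models. This lowers the weight of the point without removing it. The permutation remark is prompted by non-normal risk and protective factors, the fit check concerns the growth form, and these equations are the only specification given for this test.

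The Treatment × Year test is not touched: its slope has `u_01kp`.

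**Conclusion.** The point holds in limited form. The community-level Grade-slope equation lacks the residual that its two companions have, all three stand together in one intact block of the table, and the protocol says that "the effect of the intervention on change within communities and the relationship of grade to alcohol use is tested". Whether the test keeps its level depends on the `gamma_100p` equation, the covariance of the pair terms and the Treatment coding, none of which can be read from the text.

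Under the unfavourable readings, with a slope SD of about 0.02–0.06 and little within-pair similarity, the nominal 5% test runs at roughly 8–17% (z) or 6–13% (11 df). Under the favourable reading it is at about 5% on 11 df. A doubling or tripling is therefore one scenario, not a demonstrated property of the plan. The specification should be closed because doing so is cheap, not because an invalid analysis has been shown.

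**What to change.** Add `u_10kp` to the community-level Grade-slope equation and let it covary with `u_00kp` and `u_01kp`. Show the pair-level equation for `gamma_100p`, with its own random term. State the Treatment coding. Test `zeta_1010` against t on 11 df. `w_101p` is then redundant, because with one community per arm in a pair it cannot be told apart from the difference of the two community residuals. Keep the pair term on `gamma_100p`: with `u_10kp` alone and half the slope variance shared within pairs, the z test drops to 1.4–3.4% for slope SDs of 0.02–0.10.

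More robustly, estimate each community's Grade slope and apply a paired t-test, or a within-pair sign-flip test, to the 12 within-pair differences. The paired t-test does not depend on the coding or the random-effect covariances, and it rejected about 5% of the time in every setting tried.

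The cost is one variance term in a model already planned for MLwiN, or one short supporting analysis, and a somewhat wider confidence interval for this contrast. No new data are needed.

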## **SCIENCE-BASED PREVENTION: TESTING COMMUNITIES THAT CARE PROTOCOL AND STATISTICAL ANALYSIS PLAN**

### **Experimental Design and Methods**

In 13 of the 20 matched pairs of communities participating in the Diffusion project, neither community has progressed in the use of prevention science to the point of using tested effective policies and programs to address risk and protective factors elevated in epidemiologic community data. In the Diffusion project, these communities were matched within each state on population size, economic indicators, and crime data. Twelve pairs of these communities (24 communities) have been recruited to participate in the proposed study. One member of each pair has been randomly assigned to the CTC intervention condition; the other member of each pair has been assigned to the control group.

The intervention component will begin in the fall of Year 1, with a community activation and education process using Communities That Care training events, materials, and technical assistance. (See Appendix C for examples of the CTC community training guides from Developmental Research and Programs, the training and technical assistance subcontractor.) Intervention communities will be trained to use the baseline data collected in Year 5 of the Diffusion project, just prior to the start of the proposed study, to prioritize specific areas and risk and protective factors for attention. By the ninth month of the project, communities will select effective interventions to address their prioritized needs and create strategic community prevention plans to implement these interventions. Selected policies and programs will be offered to affect participants in the panel sample in each community beginning in the Fall of Year 2 and continuing through Year 5 of the study.

Effects of the CTC intervention on risk factors, protective factors, substance use, and other problem behaviors will be assessed using repeated cross-sectional and longitudinal student surveys in both intervention and control communities. Implementation and impact of the CTC intervention on communities' prevention service systems will be assessed using the CKI telephone interviews of community key informants, and the CRD surveys of prevention service providers in all communities.

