**Figure 1. Study Design**[figure not shown]**Study Design**

The design of the proposed research project is presented in Figure 1, above.

**Community youth samples.** Evaluation of the impact of the CTC intervention on youth outcomes (Aim 1) will include comparisons between the intervention and control communities on trends in risk, protection and drug use and related problem behaviors assessed through repeated cross-sectional surveys of all consenting 6th, 8th, 10th, and 12th grade public school students in each community conducted in 2004, 2006, and 2007 (SS in Figure 1). Comparisons also will be made between the intervention and control communities on individual student-level changes in risk, protection, and initiation of substance use, delinquency, and violence through annual surveys of a longitudinal panel of 200 fourth grade students in each community recruited in the first year of the project and followed throughout the project (Panel in Figure 1).

**Community key informant samples.** Evaluation of CTC's impact on community prevention service systems (Aims 2-4) will include comparisons between the intervention and control communities on measures of collaboration, use of epidemiological data to guide planning and resource allocation decisions, and selection of tested prevention strategies. Data on these measures will be obtained through interviews with key informants in each community conducted in 2004 and 2006 (CKI in Figure 1).

**Community prevention policy and program samples.** Information on the types, quality, and scope of prevention activities consistent with effective interventions for elementary and middle school-aged youths and their families (Aims 3 and 4) will be obtained through structured interviews with prevention service providers and program directors, also conducted in 2004 and 2006 (CRD in Figure 1).

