### **Measurement Methods, Schedules, and Instruments:**

Since 1988, the Social Development Research Group has maintained a centralized data collection unit with extensive experience in gathering data from general population and clinical samples. The unit has interviewers and supervisors with extensive experience in various aspects of data collection, including recruitment, locating, and mail, telephone, individual in-person, and school-based, group-administered surveys. Our data collection unit has been successful in maintaining high completion rates, and in providing complete data with little missingness across items.

Cross-sectional surveys. In the spring of Project Years 2, 4, and 5, all 6th, 8th, 10th, and 12th grade public school classrooms within the intervention and comparison communities will complete the youth survey used in the Diffusion project. The cross-sectional surveys will be conducted in February of each academic year by the research subcontractor in each state using scanable forms developed and printed following specifications provided by the SDRG data collection unit. This process has been used successfully in the Diffusion project to conduct the cross-sectional surveys in that project's 41 communities.

Based on our experience in the Diffusion project, we anticipate obtaining usable data from a minimum of 70% of the public school students at each of the targeted grade levels in each community. The average single grade enrollment in 2000 across these 24 communities is 316 students, resulting in an average of approximately 221 useable surveys per grade per community. To ensure high participation rates, we have provided special monetary incentives for schools that achieve a 70% participation rate.

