The effects of the elementary school interventions on risk and protective factors and early problem behavior initiation will be assessed by comparing cross-sectional sixth grade samples over time in experimental and control communities. The surveys at eighth grade (ages 13-14) provide measurement of the degree of spread of risk and problem behaviors by the end of middle school in intervention and control communities. The final eighth grade cohort (assessed in Project Year 5) will have received maximum exposure (four years) to the services implemented as a result of the CTC intervention, and the cumulative impact of the elementary and middle school interventions on the early initiation of drug use and related problem behaviors will be assessed at this grade level. The 10th grade surveys will allow detection of changes in risk, protection, and problem behaviors that result from the interventions provided during the middle school grades. Finally, the 12th grade surveys will provide a measure of community-level trends in adolescent outcomes measured at the end of high school and will allow assessment of the impact of the community-level interventions alone. This measurement design will allow for comparisons of trends across six cohorts for each age group over the five baseline years (collected in the Diffusion project) and the five years of the proposed study.

Longitudinal panel. Based on power analyses described later, a longitudinal panel of 200 students enrolled in the fourth grade in each community will be identified in the first year of the study and surveyed by SDRG data collection staff in each of the five years of the study. Representative samples of fourth grade students in each community will be recruited for participation in the longitudinal sample, and active parental consent will be obtained. Because we estimate that 280 students will be required to obtain 200 consenting panel members, the sample for the longitudinal panel will include the entire population of fourth grade public school students in the 16 communities of less than 20,000 total population in the study, and over 70% of the fourth grade students in six remaining communities. If children in this cohort in intervention communities are affected by the CTC intervention, the longitudinal panel sample should be sensitive to these effects.

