Analyses of the longitudinal panel. Use of a longitudinal panel allows examination of how the intervention affects children as individuals rather than groups over time. We expect the potentially wide variation in individual-level growth curves will be hidden in group-level analyses. The individual-level longitudinal analyses will be powerful because they can account for differences between individuals in rates of change. These longitudinal analyses will involve the use of multilevel models and growth curve modeling as described above for risks and protection, but with the longitudinal sample the growth curves will be specified at the child level rather than the community level. The effects of treatment condition on average slopes within communities will be modeled at the community level. In order for these models to work, risk and protective factors must follow a growth pattern that can be identified and modeled. Previous work has shown that it is possible to specify individual level growth curves for risk and protective factors and that differences in their slopes can be predicted by involvement in intervention (Hawkins et al., in press). Effects of the intervention on substance use and problem behavior will be examined using three level logistic models in which engaging in substance use or problem behaviors by the eighth grade is modeled as a function of the intervention.

The longitudinal panel data also will allow examination of subgroups of children most affected by the intervention. For example, students experiencing moderate to high levels of risk exposure are more likely to be affected by intervention than students experiencing low levels of risk. We will assess whether initial levels of risk and protection are differentially related to changes in risk and protection in the intervention and control groups. This can be tested using a model in which baseline risk is a covariate predicting slopes of risk at the individual level, and then assessing the effect of the intervention on this relationship at the community level. Interactions between a variety of individual level effects and the intervention can be examined in this manner to better understand for whom the intervention has the largest effects. We have an ongoing consulting relationship with [name] who will serve as an advisory board member for the proposed project and will assist in the specification of multilevel analysis models.

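### The panel is meant to measure initiation, but its model counts any engagement by eighth grade, including use already reported at the grade 4 wave before programmes began

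*Protocol*

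**What the plan says.** The Study Design section states the panel's purpose: to compare arms on "individual student-level changes in risk, protection, and initiation of substance use, delinquency, and violence through annual surveys of a longitudinal panel". The Analysis section (Aim 1, longitudinal panel) then fixes the response for substance use and problem behaviour: "engaging in substance use or problem behaviors by the eighth grade is modeled as a function of the intervention", in a three-level logistic model.

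On timing, Measurement Methods says "a longitudinal panel of 200 students enrolled in the fourth grade in each community will be identified in the first year of the study", with a survey in each of the five years. Experimental Design and Methods says programmes are offered "beginning in the Fall of Year 2 and continuing through Year 5 of the study", when the panel is in grade 5.

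The panel analysis does not exclude children who report a behaviour at the first wave, adjust for that report, or define a first-use event. The one individual baseline covariate it specifies is baseline risk, as a predictor of slopes of risk. Baseline adjustment elsewhere (baseline slopes and intercepts under Analysis, 1998 means under Power) is at community level.

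**The concern.** Take three panel children. One reports alcohol use in grade 4, one starts in grade 7, and one never uses. Under the stated response the first two are both events. Only the second began after programmes started, so only that child's initiation could have been prevented by them.

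Use that predates the programmes is expected to be equally common in both arms under randomisation. It adds the same amount to each arm's event rate and shrinks the contrast. A real effect on new initiation is understated and more easily missed, in the sample that the protocol presents as a strong test of the intervention.

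It also affects how Table 3 is read. The Power section compares detectable reductions in eighth-grade lifetime use with a 20–40% benchmark from other trials, which is stated for initiation. The two scales agree only if nobody had used before the programmes.

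**Working it through.** **Inputs from the protocol.** Table 3, eighth-grade lifetime alcohol use: prevalence p = 0.52, detectable difference 0.130 at power 0.80, stated as a 25% reduction. Final panel of about 150 per community (Measurement Methods). 24 communities in 12 pairs.

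**Assumptions.** The share q who had used alcohol before the programmes is not given, so 0.05, 0.10 and 0.20 are shown. The protocol states neither alpha nor degrees of freedom for Table 3; two-sided 5% and 10 df are assumed. The true effect is set at a 25% cut in new initiation.

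**Reproducing the plan's figures.** 0.130/0.52 = 25.0% (stated 25%). Panel size: 280 × 0.70 × 0.85 × 0.90 = 149.9 (stated about 150). The 0.130 itself cannot be rebuilt, because its variance inputs are in Appendix G, which is not shown. The standard error it implies is 0.130/(2.228 + 0.879) = 0.0418.

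**Stated rule, all children.** Ever-use by grade 8 is q plus new initiation, so a 25% cut in new initiation changes ever-use by 0.25 × (p − q).

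| q | Share of events predating programmes (q/p) | Difference | Reduction in ever-use | Power |
|---|---|---|---|---|
| 0 | 0% | 0.130 | 25.0% | 0.80 |
| 0.05 | 10% | 0.1175 | 22.6% | 0.72 |
| 0.10 | 19% | 0.105 | 20.2% | 0.62 |
| 0.20 | 38% | 0.080 | 15.4% | 0.41 |

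Power is from the noncentral t distribution with 10 df and SE 0.0418.

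**At-risk set, Wave 1 non-users.** The control rate is (p − q)/(1 − q) and the difference is 0.25 times that rate. The low power inflates the SE to 0.0418/√(1 − q); the high power keeps 0.0418. Holding the implied residual intraclass correlation (about 0.036 at 150 per community) constant gives 0.76, 0.70 and 0.58, within rounding of the high end.

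| q | Control rate | Difference | Power |
|---|---|---|---|
| 0.05 | 0.495 | 0.124 | 0.74–0.76 |
| 0.10 | 0.467 | 0.117 | 0.67–0.71 |
| 0.20 | 0.400 | 0.100 | 0.49–0.58 |

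The risk ratio in this set is 0.75 at every q; under the stated rule it is 0.77, 0.80 and 0.85.

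**Reading Table 3 on the initiation scale.** The cut in new initiation needed to produce a difference of 0.130 is 0.130/(0.52 − q): 28%, 31% and 41% at q = 0.05, 0.10 and 0.20. The last is just above the top of the 20–40% benchmark.

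**The case against.** **Any use by eighth grade is a legitimate randomised contrast.** It compares all panel children by assigned arm and matches the lifetime measures in Table 3. This stands. It is a reason to keep the outcome under its own name, but it does not make it a measure of initiation.

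**The size is speculative.** Grade 4 use is undocumented and may be low. The SE comes from eighth-grade survey data with a 1998 community covariate and is carried over to a different sample. Both points stand. The fair measure of the rule's cost is stated rule against fix, for example 0.62 against 0.67–0.71 at q = 0.10, and not the fall from 0.80. Most of that fall remains after the fix when q is small.

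**At-risk sets belong in a later plan.** This would be a good answer if the protocol had left the response open. It states a response, and that response differs from the target named in Study Design.

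**Wave 1 may not precede CTC itself**, since community activation starts in the fall of Year 1. That is so, but it does precede delivery of programmes to children.

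**A reader might extend the point to the cross-sectional surveys**, because that section lists "initiation of alcohol, cigarette, and marijuana use, and incidence of delinquent and violent behavior" and proposes "combining grade level samples and entering grade as a covariate at the child level 1". The documents do not support the extension. The example there is "reported alcohol use, a child level dependent variable at a single time point", with no recall period, and the longitudinal form is described as prevalence. Tables 2 and 3 include 30-day measures, so it cannot be said that every surveyed grade is scored as ever-use. The combined model places treatment on the year and grade slopes, so the Year 2 cells serve as reference for change and should not be dropped. Measurement Methods also gives the 12th-grade surveys a different purpose, community-level trends.

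**Conclusion.** The point holds for the longitudinal panel. The stated target is initiation, while the stated response is any engagement by eighth grade in all children, so use from before the programmes is counted as an event. The direction is certain: an effect on new initiation is diluted by the factor (p − q)/p. The size rests on q, which the document does not give. At 5% prior use the fix gains 2 to 4 percentage points of power; at 20% it gains 8 to 17. If grade 4 use is small, so is the effect. Only alcohol is tabulated here, and the size will differ by behaviour.

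A reader might infer that the panel result would be biased toward finding a benefit, or invalid. Neither follows: the consequences are reduced sensitivity and a label that does not match the quantity estimated.

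**What to change.** In the panel part of the Aim 1 analysis:

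1. For each behaviour, define initiation as the first report after Wave 1 among children who reported none at Wave 1.
2. Analyse it with a discrete-time (wave-by-wave) multilevel logit in the same student, community and pair structure, so that each child contributes until first report or loss.
3. Keep any use by eighth grade in all children as a separately named prevalence outcome.
4. Say in the Power section that Table 3 concerns prevalence, and that the matching reduction in new initiation is larger whenever some children used before the programmes.

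No new survey wave is needed. Panel members tracked to the end must have completed the first two waves, so Wave 1 status should be available, provided the version of the survey adapted for grades 4 and 5 keeps the use items. The costs are a somewhat smaller at-risk set that differs by behaviour, and reliance on fourth-grade self-report to define it. The cross-sectional model needs no change on this account.
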